## Background

### Study setting

The study will be conducted in the Kaushambi district in UP. Out of the district's eight community development blocks, the m-health intervention has been implemented in two blocks: Mooratganj and Manjhanpur.

The Catholic Relief Services (CRS) with the help of a local NGO, Vatsalya, introduced the CommCare m-health application to 259 ASHAs in the two intervention blocks in 2012. The ASHAs in the ReMiND project were provided with basic Java-based mobile phones operating on open source CommCare software (15). Extensive trainings of ASHAs were done in both blocks on the use of these phones. The ReMiND application has tailored content and guides the ASHA through the course of a woman's pregnancy and newborn child care. ASHAs use the application for the following purposes:To register each pregnant womanTo update her ANC record during home visits on the mobile applicationTo track her from pregnancy into the postpartum periodTo track the health of the newbornTo track the status of routine immunization until 2 years of ageTo provide appropriate counseling and support at each of these stepsThe phones contain locally relevant audio and visual prompts to help ASHAs navigate through the application. These recordings and pictures enrich the counseling experience of ASHAs during their home visits. The application uses the data entered about the pregnancy to guide ASHAs in providing timely and appropriate health information; it helps them to prioritize home visits; and it employs algorithms to assist in the early identification, treatment, and rapid referral to appropriate care of any danger signs among pregnant women or neonates (Fig. 1). While ASHAs have many tasks assigned to them, the key one is to identify pregnant women and visit them throughout the course of their pregnancy, seeing them through delivery in a safe facility and appropriate newborn care.

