### Overview of study design

The study has been approved by the Institute Ethics Committee of the Post Graduate Institute of Medical Education and Research, Chandigarh, India. Written informed consent will be obtained from all study participants. Administrative approval will be obtained for collection of relevant data.

We will use a quasi-experimental design comprising pre- and post-intervention observations with a control to assess the impact of the ReMiND project. Data from the Annual Household Survey (AHS) undertaken by the Registrar General of India in district Kaushambi in 2011 will be used for baseline or pre-intervention assessment (4). The AHS is the largest demographic survey in the world and covers two and a half times that of the Sample Registration System (India's most regular source of demographic statistics). The sampling design adopted for the AHS is a uni-stage stratified simple random sample without replacement, except in case of larger villages in rural areas (i.e. having a population greater than or equal to 2000 as per 2001 census), wherein a two-stage stratified sampling procedure has been applied. The details of the AHS survey are incorporated in the supplementary material.

We will undertake a cost-effectiveness analysis household (CEAHH) survey in 2015 in two intervention blocks and two control blocks from the Kaushambi district to assess the coverage of various MNCH services that represent the post-intervention status. To carry out the CEAHH survey, two structured interview schedules were developed after an extensive review of existing tools used in AHS, the National Family Health Survey, the District Level Household Survey, and the Coverage Evaluation Survey.

Together, the AHS and the CEAHH will be used to assess the impact of the ReMiND m-health intervention using a difference in differences (DID) analysis. To reduce selection bias, before DID is performed, propensity score matching (PSM) will be used to match the cases from the intervention blocks with those in the control group based on their socio-demographic characteristics, for the period between 2011 and 2015 (4). Further, subgroup analysis will be done to analyze the impact of intervention among various levels of underlying factors, such as the mother's education and the occupation of the head of household.

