### Study area

The study area for the CEAHH survey will be two intervention and two control blocks out of a total of eight community development blocks in the Kaushambi district. The two control blocks will be selected based on matching for three health service utilization indicators: average number of ANC checkups, percentage of women receiving three or more ANC checkups and percentage of institutional deliveries.

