### Sampling

The primary sampling unit (PSU) for the CEAHH survey will be a village. For selection of PSUs, a list of all villages from the two intervention and two control blocks will be prepared. From all villages in Kaushambi, 10% of each will be selected from the intervention area and the control area. This means that 69 PSUs each will be selected randomly from the intervention and control areas, using the probability proportional to size method.

In each PSU, a household enumeration will be undertaken to identify all mothers with a child in the age group of 29 days to 6 months, or between 12 and 23 months on the date of the survey. This list will serve as the sampling framework to randomly select the required number of mothers in each category for interview. The number of clients to be interviewed per PSU will again be selected by the probability proportional to size method and will be determined based on the relative size of the PSU.

The clients (mothers with a child in the 29 days to 6-month or 12- to 23-month age range) within each PSU will be selected using systematic random sampling. If more than one child in the respective age category is present in a given household (i.e. more than one child is between 29 days and 6 months or more than one child is between 12 and 23 months), then one will be randomly selected. If the family has one child in the 29 days- to 6-month range and one in the 12- to 23-month range, then both children would be part of the sampling frame and would have the same probability of being selected as would any other child in the sampling frame.

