Additionally, mothers in both categories will be interviewed in the intervention and control area about the extent and quality of services offered by the ASHAs during the antenatal and postnatal home visits. Specific questions will be posed to mothers in the intervention area to assess the usage of the mobile application and their satisfaction with this mobile-assisted counseling.

### 
Data analysis

DID will be the primary analysis and will be based on the AHS and CEAHH data from intervention and control areas. Propensity scores will be used to match the women of intervention area with control area based on their socio-demographic characteristics. This will help to reduce the selection bias by taking into account the variation caused by known confounders. The AHS dataset for analysis comprises a total of 450 women: 225 from the intervention areas and 225 from the control areas. The CEAHH data have 1,053 women with a child aged 1–6 months each in intervention and control area. Similarly, a total of 1,391 women with a child aged 12–23 months in intervention and control area are part of the CEAHH dataset.

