(a) PSM: The non-random choice of the two intervention blocks could result in selection bias. In order to minimize this bias, the PSM method will be used to control for demand-side characteristics that could influence utilization of various MNCH services. The PSM approach attempts to render the effects of different observed covariates X on participation as a single propensity score or index defined byP(X)=Pr(T=1∣X).The idea is to find, from a large group of control area women, those who are observationally similar to the intervention area women in terms of characteristics that are unaffected by the m-health intervention but that influence the utilization of key MNCH services (25). Then, each woman in the intervention arm will be matched with a woman in the control arm who is observationally similar (e.g. on socio-economic characteristics like literacy rate, caste, occupation of the mother, and age). The PSM estimator for the treatment effect on the treated can be specified as the mean difference of Y (i.e. institutional delivery or full immunization, or any other key indicator under consideration) over the usual support, weighting the comparison units by the propensity score distribution of eligible women in the respective categories. A typical cross-section estimator can be specified as follows:$$TOT_{PSM}=E_{P(x)|T=1}\{E[Y^{T}|T=1,P(X)]-E[Y^{C}|T=0,P(X)]\}.$$

(b) DID: This method essentially compares intervention and control groups in terms of outcome changes over time relative to the outcomes observed for a pre-intervention baseline. That is, given a two-period setting where *t*=0 before the program and *t*=1 after program implementation, letting $Y_{t}^{T}$ and $Y_{t}^{C}$ be the respective outcomes for a program beneficiary and non-treated units in time *t*, the DID method will estimate the average program impact as follows:$$DID=E(Y_{1}^{T}-Y_{0}^{T}|T_{1}=1)-E(Y_{1}^{C}-Y_{0}^{C}|T_{1}=0)$$In equation (1), *T*_1_=1 denotes treatment or the presence of the program at *t*=1, which is evaluated from CEAHH data, whereas *T*_1_=0 denotes absence of the program, which is evaluated using AHS data. Outcomes in the form of coverage of key MNCH services such as ANC, immunization and institutional deliveries will be assessed (25). Along with the above techniques, for each primary and secondary outcome, the estimated effect size and confidence intervals will be estimated to indicate the levels of precision.

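### The difference-in-differences is stated by area and period only, so a change between surveys in the mix of the two blocks within an area would enter the effect estimate; the likely cost is mainly extra variance, of unknown size

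*Protocol article*

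**What the plan says.** - **Areas and blocks.** Study setting: "the m-health intervention has been implemented in two blocks: Mooratganj and Manjhanpur". Study area: "The two control blocks will be selected based on matching for three health service utilization indicators". Each area in the comparison is therefore a pair of blocks.
- **Estimator.** Data analysis, part (b): "This method essentially compares intervention and control groups in terms of outcome changes over time relative to the outcomes observed for a pre-intervention baseline". The equation that follows has a treatment index and a period index and no term for block.
- **Matching.** Data analysis and its part (a) base the propensity score on the woman's socio-demographic characteristics. Block is not among the variables listed.
- **2015 survey (CEAHH).** Sampling: "69 PSUs each will be selected randomly from the intervention and control areas, using the probability proportional to size method". No block stratum or quota is given. Within villages, "The number of clients to be interviewed per PSU will again be selected by the probability proportional to size method". No sampling weights are mentioned.
- **2011 survey (AHS).** Overview of study design: "The sampling design adopted for the AHS is a uni-stage stratified simple random sample without replacement", with a two-stage variant for larger villages. The strata are not named, and the detail is in a supplement that is not shown. The analysis set is given only as "225 from the intervention areas and 225 from the control areas".
- **What the DID is meant to do.** The limitations in the Discussion assign household-level, demand-side confounding to matching, and supply-side health system factors to the DID.

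**The concern.** Supply-side factors can differ between the two blocks of one area. Differencing area means removes such level differences only if the two blocks carry the same weight in both rounds. The women interviewed in 2011 and 2015 are different people, drawn under two different designs, and nothing in the stated plan holds the block mix constant. If the better-covered block makes up more of an area's sample in 2015 than in 2011, the area appears to improve although neither block has changed. That apparent change would be read as programme effect in the intervention area, or subtracted as secular trend in the control area. The DID would then fall short on the factors that the Discussion relies on it to remove.

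**Working it through.** **The plan's own figures.** The sample sizes reproduce with the two-proportion formula, unpooled variance, two-sided 5%, 80% power (z-sum squared 7.849):
- 18.9% vs 23.9%: (0.189×0.811 + 0.239×0.761) × 7.849 / 0.05² = 1,053.
- 30.8% vs 35.8%: (0.308×0.692 + 0.358×0.642) × 7.849 / 0.05² = 1,391.

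The target is thus a 5-point difference, and that is the yardstick below.

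**The composition term.** Let w0 and w1 be the sample share of block A in an area in 2011 and 2015, and pA and pB the coverage of its two blocks, held constant over time. The area mean changes by (w1 − w0)(pA − pB). The DID contains this term for the intervention area minus the same term for the control area.

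Illustrative values for a shift in one area only (the article gives no block figures):
- share shift 5 points, gap 5 points: 0.25 points
- 10 and 10: 1.0 point
- 10 and 20: 2.0 points
- 20 and 20: 4.0 points

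**Chance shift in shares.** Assumptions: two blocks of equal size, villages falling independently into either, 69 villages in 2015 (Sampling), and k AHS villages per area (not given; taken as 10 to 20).

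SD of the share shift = √(0.25/k + 0.25/69).
- k = 10: √(0.0250 + 0.0036) = 0.169
- k = 20: √(0.0125 + 0.0036) = 0.127

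With a 10-point gap this is 1.7 or 1.3 points per area. Multiplying by √2 for two areas gives 2.4 or 1.8 points of SD in the DID. With a 5-point gap the figures halve to 1.2 and 0.9.

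If the AHS split is fixed, only the 2015 part remains: √(0.25/69) = 0.060, so 0.6 points per area and 0.85 points in the DID at a 10-point gap.

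**Effect on the standard error.** Simulation of the pooled DID against the DID with block terms (225 and 1,053 women per area, 69 villages in 2015, 30% coverage, village SD 8 points, 2,500 runs):
- 10-point gap: 6.6 vs 6.1 with 10 AHS villages; 5.9 vs 5.7 with 20.
- no gap: 6.09 vs 6.15 with 10; 5.57 vs 5.58 with 20.

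A second simulation of 4,000 runs gave 6.6 vs 6.2 and 5.8 vs 5.5 at the 10-point gap. Adding variances as a check: √(6.1² + 2.4²) = 6.6 and √(5.7² + 1.8²) = 6.0. The increase is about 3 to 8% at a 10-point gap. At 5 points it is 1 to 2%: √(6.1² + 1.2²) = 6.2 and √(5.7² + 0.9²) = 5.8.

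**A possible systematic shift.** Choosing villages in proportion to size and then setting interviews in proportion to size gives each village an unweighted share that rises with size squared. Take two blocks of equal population with assumed village sizes 2,500 and 1,500. The number of villages in a block is proportional to 1/size, so its unweighted share is proportional to size: 2,500/(2,500 + 1,500) = 62.5% instead of 50%. If the AHS share is 50%, a 10-point gap gives 12.5% × 10 = 1.25 points in the DID.

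**The case against.** Several objections have force.

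- **The AHS design is not visible.** A reader might infer that neither survey fixes the block split. The article does not support that: the AHS is described as stratified and its strata are not named. The point matters, because the AHS term supplies 87% of the share variance at k = 10 (0.0250/0.0286) and 78% at k = 20 (0.0125/0.0161). Even the 2015 term could be smaller if villages are drawn systematically from a list ordered by block; the variant is not stated.
- **The block gap is assumed.** All four blocks lie in one district, and matching would already reduce any part of a gap that reflects socio-demographic differences.
- **A reader might take this as demonstrated bias.** It is not. In two properly weighted probability samples, block shares equal population shares in expectation, and a chance shift adds variance only. A systematic shift needs the doubly size-proportional 2015 sample to be analysed unweighted, which the article neither says nor excludes.
- **The simulated gain is small.** The block-term standard error should not depend on the gap, yet with 20 villages it varies between 5.5 and 5.7 across settings. A gain of 0.2 is no larger than that noise.
- **An article may leave model terms and weights to a full plan.** This is true, and the sentence quoted on the estimator is a general description of the method. However, the article does write out its estimator and its village draw, both at area level, and then relies on that estimator for supply-side factors. The point concerns those stated choices and does not depend on missing detail.

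**Conclusion.** The point holds as a conditional weakness. As stated, the DID is pooled over blocks, block is not a matching variable, and the 2015 village draw has no block stratum. Any difference in block shares between rounds, combined with a coverage gap between the blocks of an area, therefore enters the estimate.

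Its size cannot be determined from the article. Under an assumed 10-point gap and 10 to 20 AHS villages per area with an unfixed split, it adds 1.8 to 2.4 points of SD to the DID, or about 3 to 8% to the standard error. With a fixed AHS split it adds about 0.85 points, roughly 1% (√(6.1² + 0.85²) = 6.16). The effect is mainly lost precision, with a systematic component possible only under an unweighted 2015 analysis. It is not a demonstrated error in the result. It still merits a change, because the remedy uses data already held and costs almost nothing if the blocks do not differ.

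**What to change.** - **Model.** Fit the DID as a regression on the matched samples with fixed effects for the four blocks (these absorb the area main effect), a period term and the area-by-period term. Alternatively, weight both rounds to the same block shares. Either sets w1 = w0 in effect and removes the level-composition term. Area is defined by block, so block should be known for every woman in both surveys.
- **Village draw.** If the 2015 villages have not yet been drawn, allocate the 69 per area to the two blocks in proportion to population before selection. The article uses both future and present tense for this survey, so the draw may already be complete; the model change does not depend on it.
- **Reporting.** Give the number of women per block in each round. Block-specific changes may be shown descriptively, but not as matched block pairs: Study area describes selecting two control blocks by matching and defines no one-to-one pairs. The AHS sample would also average only about 112 women per block (225/2).

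The cost is one model line and, where still possible, a stratified draw from the same village list. The planned 1,053 and 1,391 do not change. Block terms do not remove differences between blocks in trend or in effect, and they do not repair the imprecision that comes from 225 baseline women per area.

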### Quality control

Data quality will be assessed during the survey as adherence to the sampling plan, correctness, completeness and accuracy of data. With these aspects of quality in mind, a team of supervisors will monitor the sampling techniques followed by field investigators while collecting the data. During the quality visits, 10% of the data collected by each investigator will be collected again by the supervisor and further analyzed to check for discrepancies. If a wide range of discrepancies within or across investigators or items is found, a standard set of procedures, for example, validation or repeat sampling procedures, will be followed to resolve the same. Missing data will be imputed with the standard regression imputation technique.

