### Sample size

Two categories of individuals will be identified in each PSU: 1) women with one or more children aged 29 days to 6 months and 2) women with one or more children aged 12–23 months. The sample size for each category was estimated with respect to differences in coverage of two key MNCH services (institutional delivery and full immunization coverage) and neonatal and child morbidity rate for severe disease. For mothers with children in the younger age group, neonatal and child morbidity rates and institutional delivery coverage were used to determine sample size. For mothers with children in the older age group, the difference in rates of full immunization coverage was used to assess sample size.

We determined the sample size required to detect a 5% change in the coverage of MNCH services and neonatal and child morbidity rates, with a power of 80% and an alpha error of 5%. Baseline coverage of 15.1% and 30.8% for institutional delivery and full immunization coverage in control area, respectively, was assumed (18). Similarly, a neonatal morbidity rate of 18.9% for severe neonatal disease was assumed in the control area (4). With these parameters, sample sizes of 1,053 women with a child in the younger age group and 1,391 women with a child in the older age group from the intervention and control areas, respectively, were considered appropriate.

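### The plan names standard regression imputation and promises confidence intervals, but nothing carries imputation uncertainty into them, so they will be somewhat too narrow

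*Protocol article*

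**What the plan says.** The Quality control section of the protocol article has one sentence on missing data: "Missing data will be imputed with the standard regression imputation technique". It gives no expected missing-data rate and does not list the variables to be imputed. It does not say whether the model is linear or logistic, or whether one or several completed data sets will be made.

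The Data analysis section sets the main estimate: "DID will be the primary analysis and will be based on the AHS and CEAHH data from intervention and control areas". Propensity score matching comes before it. The outcomes are coverage indicators, given as "institutional delivery or full immunization, or any other key indicator under consideration"; the two named are yes/no for each woman or child. On precision, part (b) of that section says that "for each primary and secondary outcome, the estimated effect size and confidence intervals will be estimated to indicate the levels of precision". The article mentions no multiple imputation, no variance correction for imputed values and no missing-data sensitivity analysis.

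**The concern.** In ordinary usage, regression imputation fills each gap with the value predicted from a fitted model. The filled value has no residual variation, and the fitted model is treated as known. If the completed file then goes through matching and DID as though every value had been observed, the analysis counts more information than was collected. The standard error is too small and the interval too short.

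The article says the intervals are there to show precision, so this weakens the purpose they are given. This is a method that the article itself fixes, not a detail left open. At stake is how firmly a coverage effect can be claimed when the design targets a change of 5 percentage points.

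**Working it through.** **Inputs from the article**
- Sample size section: "sample size required to detect a 5% change in the coverage of MNCH services", power 80%, alpha 5%; "Baseline coverage of 15.1% and 30.8% for institutional delivery and full immunization coverage in control area"; severe neonatal morbidity 18.9%.
- Data analysis section: 225 + 225 women at baseline (2011 survey, AHS); 1,053 + 1,053 women with a younger child afterwards (2015 survey, CEAHH).

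**Assumptions, because the article gives no figure**
- Missing share r = 2%, 5%, 10% or 20%, completely at random.
- Weak predictors.
- Institutional delivery at 15.1% in three cells and 20.1% in the post-intervention cell, so the true DID is 5 points.
- No clustering and no matching.

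**1. Reproduce the planned sample size.** Two proportions, unpooled variance, two-sided: n = (1.96 + 0.8416)² × [p₁(1−p₁) + p₂(1−p₂)] / 0.05².
- 18.9% to 23.9%: 7.849 × 0.33516 / 0.0025 = 1,053 after rounding up.
- 30.8% to 35.8%: 7.849 × 0.44297 / 0.0025 = 1,391 after rounding up.

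Both match the article. The imputation point does not affect them.

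**2. DID variance with complete data.**
- Baseline part: 2 × 0.151 × 0.849 / 225 = 0.001140.
- Post part: (0.151 × 0.849 + 0.201 × 0.799) / 1,053 = 0.000274.
- Total 0.001414, so SE = 0.0376. The baseline part is 0.001140 / 0.001414 = 81% of the total.

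**3. All four cells imputed.** With weak predictors, each imputed value sits close to its cell mean. The reported variance of a cell mean is about (1−r)pq/n. The true variance is pq/[n(1−r)]. So reported SE / true SE = 1−r, and coverage = 2Φ(1.96(1−r)) − 1.

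| Missing | SE ratio | Coverage |
|---|---|---|
| 2% | 0.98 | 94.5% |
| 5% | 0.95 | 93.7% |
| 10% | 0.90 | 92.2% |
| 20% | 0.80 | 88.3% |

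The half-width with complete data is 1.96 × 0.0376 = 7.4 points. At 10% missing, about 7.0 points are reported against 7.8 valid; at 20%, about 6.6 against 8.2.

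**4. Only the 2015 survey imputed.** Reported variance = 0.001140 + (1−r) × 0.000274. True variance = 0.001140 + 0.000274/(1−r).

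| Missing in 2015 | SE ratio | Coverage |
|---|---|---|
| 5% | 0.990 | 94.8% |
| 10% | 0.980 | 94.5% |
| 20% | 0.957 | 93.9% |

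**5. Simulation of the four-cell case** (1,500 replicates, robust SE, area-by-survey term in the imputation model), at 2%, 5%, 10% and 20% missing:
- Unrounded linear prediction: coverage 95.0%, 93.4%, 92.9% and 87.1%.
- A single random draw per gap: 94.5%, 93.6%, 92.9% and 90.1%.
- Complete cases: about 95% throughout.

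With 1,500 replicates the simulation error is about √(0.95 × 0.05/1,500) = 0.6 points.

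**6. Bias.** In the same simulation, unrounded linear imputation left the mean DID at 0.050 with 20% missing (true value 0.05). Rounding imputed values to 0 or 1 lowered it to about 0.044 at 10% and 0.040 at 20%. Separately, if the model has no area-by-survey term and a share r is missing in every cell, the imputed values add nothing to the DID. The estimate then becomes (1−r) × 5 points: 4.5 at 10% and 4.0 at 20%.

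**The case against.** The sentence does not say that imputation is single, that the model is linear, or that outcomes are imputed. Stochastic or multiple regression imputation is not strictly excluded, and a condensed article commonly leaves the model form and variable list to a fuller document. That is fair, and the absence of those details is not the point here. What remains is that the method the article names, in its ordinary meaning, does not give valid intervals without a further step. Reading it as a single random draw does not rescue it, since that also under-covered at 20% missing.

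The four-cell figures are a worst case. The sentence sits in a section about monitoring the 2015 fieldwork, and if only that survey is imputed the loss almost vanishes, because the baseline women carry most of the variance. Missingness may also be low: this is a one-time interview, mothers' recall replaces an absent immunization card, supervisors re-collect 10% of each investigator's data, and repeat sampling is available. All of this stands, and it is why the size is given as a range.

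A reader might infer that the method is unsuitable for binary outcomes, or that it will pull the effect toward zero. The article does not support either. A logistic model is also regression imputation, unrounded linear imputation left the DID unbiased in the check, and nothing in the article proposes rounding or leaving out the area-by-survey term.

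**Conclusion.** The point holds in a limited form. Followed in its ordinary sense, the stated method gives intervals for the DID that are somewhat too narrow. At 5% to 20% missing, coverage runs from 94.8% down to 93.9% if only the 2015 survey is imputed, and from 93.7% down to 88.3% if all four cells are. At about 2% it is negligible either way. The loss is material only near 20% missing in both surveys.

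These figures assume weak predictors, data missing completely at random, and no clustering or matching. Better predictors would reduce the loss. Attenuation is a risk to guard against in the specification, not an error that the article commits. The planned sample sizes are unaffected.

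**What to change.** Replace the sentence in Quality control with multiple imputation, or another method whose variance is valid.

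- State which variables are imputed, and in which survey.
- Use logistic models for binary items.
- Include area, survey, their interaction, the outcomes and the propensity score covariates in the imputation model.
- Estimate the propensity score, match and compute the DID within each completed data set, then combine with Rubin's rules.
- Report the missing share by area and survey, and give the complete-case DID as a sensitivity analysis.

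This needs no new data and runs in standard software. The cost is some extra analysis time and slightly wider intervals.
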